### Eligibility criteria

Inclusion criteria will be selected for the following participants:Diagnosis of knee OA and consideration of primary unilateral TKAConsidering primary and unilateral TKAHave already trialled nonoperative management for their knee symptomsAre willing and able to use web or mobile phone-based prognostic tool interfacesAble to provide informed consent to participate and available to be followed up for the duration of the study

The exclusion criteria were as follows:The source of knee symptoms are considered to be from any cause other than knee OA, e.g., rheumatoid arthritis, inflammatory arthritis, hip OA, referred lower back pain, etc.Are considering bilateral TKA, revision TKA, unicondylar knee arthroplasty, or patellofemoral arthroplastyTKA on the contralateral sidePrior history of septic arthritis in the affected kneeSignificant bilateral knee symptomsIntra-articular injection in the affected knee within the last 3 months

### Randomisation, allocation, and blinding

Participants will be randomly allocated in a 1:1 ratio into two groups: intervention and treatment as usual (TAU). Allocation will be performed using a computer-generated simple randomisation schedule of consecutive patients. The randomisation will be embedded into the web-based platform that hosts the study portal. All participants who meet the eligibility criteria will be randomised.

Due to the nature of the study, participants will remain unblinded from their allocation group. However, limited disclosure of allocation groups will be applied to prevent participants who are allocated to TAU from proactively seeking out online prognostic tools to use. Investigators (excluding research assistants who will not be involved in data analysis) will remain blinded to the allocation group and identity of patients until after final data analysis is performed. Surgeons will be blinded to the allocation group of their patients and will have no influence on the outcome of allocation or intervention.

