### Study design and setting

This is a prospective, pragmatic, assessor-blinded, superiority randomised controlled trial evaluating participants who have been diagnosed with knee OA and are considering TKA. Participants will be recruited from two sources: St. Vincent’s Hospital Melbourne (SVHM) Orthopaedic Outpatient Clinic and HCF (private health insurance company) client base across Australia.

From the SVHM source, patients who have been referred to an orthopaedic surgeon for consideration for TKA will be targeted for recruitment. This information can be found on clinic appointment lists in advance of 3 months. Patients who are referred to the clinic often wait up to 1 year to be seen by an orthopaedic surgeon. Following consultation, if deemed appropriate for surgery, patients may wait for another 6–12 months before the surgery is performed. Often, patients who are seen at SVHM are already in the later stages of the TKA journey as a product of resource constraints and waiting lists at the hospital.

In comparison, patients from the HCF source are at various stages of the TKA journey. As expected, some patients may be very early in disease progression, with symptoms being adequately managed by their general practitioner (GP). However, other patients may be more advanced in their disease progression and may have already made an application for TKA funding. Potential participants here will be recruited from internal advertising.

Having a diverse recruitment pool with patients at all stages of the TKA journey can help us evaluate the optimal timepoint for *SMART Choice* tool usage. We hypothesise that patients earlier in the TKA journey may be more open to decision making with consideration of predicted outcomes. In contrast, patients who are further along the TKA journey may feel too invested for the tool to influence decision making around willingness for surgery. The optimal timepoint for *SMART Choice* tool usage will be evaluated from a sub analysis of patients at different timepoints in the TKA journey.

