**Fig. 1 Fig1:**
[figure not shown]
Screenshot of the *After My Surgery* tool for displaying predicted outcome after prognostic tool use. The *SMART Choice* tool will use a similar display format

Participants in the TAU group will receive standard care for TKA consideration without *SMART Choice* tool use. This includes clinic appointments, education packages, and booking/performance of TKA if clinically appropriate. TAU care will vary between institutions.

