### Sample size and recruitment

Previous studies have estimated baseline willingness for surgery in TKA candidates to be approximately 70% [31]. With the use of first-line interventions, such as therapy groups, willingness to undergo surgery was reported to decrease by 35% at 12 months [32]. We expect our cohort to have a lower baseline willingness for surgery, considering that we will have a significant proportion of participants recruited at the earlier (and less severe) stage of knee OA. We also expect our tool to have a greater impact on willingness to undergo surgery, especially for participants who were earlier in the TKA journey. To detect an absolute change in willingness to undergo surgery from 65 to 50%, a sample size of 169 participants in each arm was required based on calculations using a two-sided t-test at the 5% level of significance with 80% power. To account for a higher-than-expected loss to follow-up proportion due to the online nature of the tool, a 20% inflation of the sample size was added. This resulted in a target enrolment of 200 participants in each arm for a total sample size of 400 participants.

The sample size calculated is a feasible number to recruit because SVHM performs approximately 400 TKAs each year, and HCF has approximately 50,000 members with knee OA. We will aim to recruit 200 patients from the SVHM cohort and approach a random pool of 200 patients with knee OA from the HCF client database. Based on these calculations, we estimate that 6 months will be sufficient time for recruitment to be completed, with a total study time estimate to be 21 months (Fig. 3).

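### Simple randomisation forgoes balance by recruitment source that the study portal could secure at almost no cost; stratify by source and carry source into the primary analysis

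*Protocol article*

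**What the plan says.** All references are to the protocol article.

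- **Allocation.** Under Randomisation, allocation, and blinding: "Participants will be randomly allocated in a 1:1 ratio into two groups", and "Allocation will be performed using a computer-generated simple randomisation schedule of consecutive patients". No stratification factor or blocking is named. The same section adds: "The randomisation will be embedded into the web-based platform that hosts the study portal".
- **Sources and stage.** Under Study design and setting: "Often, patients who are seen at SVHM are already in the later stages of the TKA journey". By contrast, "In comparison, patients from the HCF source are at various stages of the TKA journey", and some of these are very early. The section also hypothesises that earlier-stage patients are more open to influence from the tool.
- **Stage and willingness.** Under Sample size and recruitment: "We expect our cohort to have a lower baseline willingness for surgery". The reason given is the share of participants at an earlier, less severe stage. The planned split is 200 from SVHM and 200 from HCF.
- **Analysis.** The Statistical plan compares categorical outcomes by chi-squared test and reports a relative risk. Logistic regression with odds ratios is used only if variables associated with willingness turn out imbalanced. Recruitment source is not named.

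**The concern.** Recruitment source is a planned half-and-half split. Through journey stage, the article ties it to the level of the primary outcome. One unrestricted schedule does not hold the arms equal within a source, so a chance difference in source mix feeds straight into the crude comparison of willingness.

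The usual reason to accept this is that simple randomisation keeps the next assignment unpredictable. That reason is weak here, because allocation is automated in the portal and runs straight after electronic consent. Source is also known beforehand: each participant enters through an individual emailed link, and the ethics approval and data server already depend on source.

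What is at stake is balance, some precision and the credibility of the crude comparison. The validity of the trial is not at stake.

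**Working it through.** **Inputs from the article:** 1:1 simple allocation; 200 SVHM and 200 HCF; willingness 65% against 50%; two-sided 5% level; 80% power; unadjusted chi-squared test.

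**Assumed, because the article gives no rate by source:** a willingness gap between sources of 10, 20 or 30 points, centred on 65%, with the same absolute effect in both sources and all 400 analysed.

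**1. The plan's own figure.** For 65% against 50%, the mean proportion is 0.575. With pooled variance:

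n = [1.96·√(2 × 0.575 × 0.425) + 0.842·√(0.65 × 0.35 + 0.50 × 0.50)]² / 0.15² = 169.3 per arm.

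The stated 169 reproduces. With all 200 per arm analysed, power is about 86%.

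**2. Size of the chance imbalance.**
- The intervention count within one source is Binomial(200, 0.5), with SD √(200 × 0.25) = 7.07 and a 95% range of 86 to 114.
- The SVHM share in each arm has an average of 0.5 over about 200 people. The difference in share between arms has SD ≈ √(1/400) = 0.05. Simulation of 400,000 allocations gave 0.050.
- In that simulation the difference reached 5 points or more in about 34% of trials, 10 or more in about 5%, and 15 or more in about 0.3%.

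**3. Effect on the crude comparison.** Shift = imbalance × source gap.

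| Assumed gap | Shift at 1 SD (5 points) | Shift at 10 points |
|---|---|---|
| 10 points | 0.5 | 1 |
| 20 points | 1.0 | 2 |
| 30 points | 1.5 | 3 |

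For scale, the target effect is 15 points and the standard error of the difference is √[(0.2275 + 0.25)/200] = 4.9 points.

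**4. Type I error and power.** These were simulated with at least 200,000 trials per scenario; the adjusted test is Mantel-Haenszel stratified by source.

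| Gap | Simple, unadjusted: type I / power | Simple, adjusted: power | Stratified, unadjusted: type I | Stratified, adjusted: type I / power |
|---|---|---|---|---|
| 10 | 5.0–5.1% / 86% | 86% | 4.9% | 5.0% / 86% |
| 20 | 5.1% / 86% | 87% | 4.5–4.6% | 4.9–5.0% / 87–88% |
| 30 | 5.1% / 86% | 89% | 3.9–4.0% | 5.0% / 89% |

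**5. Why stratifying without adjusting is conservative.** The chi-squared test uses the overall variance, 0.65 × 0.35 = 0.2275. Once the arms are balanced by source, only the within-source variance remains. At a 30-point gap (80% and 50%) that is (0.16 + 0.25)/2 = 0.205. The effective critical value becomes 1.96 × √(0.2275/0.205) = 2.06, a two-sided level of 3.9%, in line with the simulation.

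**The case against.** The strongest reply is that nothing here is invalid. Simple randomisation is unbiased, and the test and confidence interval already allow for chance imbalance. Type I error stays at about 5% for every gap examined, and at 400 participants a large imbalance is uncommon. All of this stands.

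The assumed gap may also be generous. If SVHM patients resemble the published candidates at about 70% willing, and the whole cohort is at 65%, then HCF is at about 60% and the gap is 10 points. A 10-point imbalance would then shift the estimate by only 1 point. This stands too, and it is why the range starts at 10.

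The Statistical plan does offer regression if imbalance appears. This answers only part of the point: the adjustment depends on what is observed, does not name source, and changes the reported measure from a relative risk to an odds ratio.

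A reader might infer more than the article supports, in three ways:
- **That it predicts different willingness, tool effect and usual care for SVHM and HCF.** It does not do so by source. The willingness statement compares the whole cohort with published studies, and the expected difference in response is by stage. The remark that "TAU care will vary between institutions" (Intervention and comparison groups) is not a contrast of SVHM with HCF, since HCF is an insurer whose clients are spread across Australia.
- **That uneven arms within a source damage the timing question.** That analysis is planned by journey stage, not within source. Even an 86/114 split keeps 4 × 86 × 114 / 200² = 98% of the efficiency of an even split.
- **That the likely distortion is a fifth of the target effect.** The 3-point figure combines a 1-in-20 imbalance with an assumed 30-point gap.

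**Conclusion.** The point holds as a missed precaution, not as an error of validity. The article fixes an unrestricted schedule although a prognostically relevant split is known before allocation and the portal could balance it.

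The imbalance figures follow from 200 per source and 1:1 allocation: SD 5 points, and 10 points or more in about 5% of trials. The resulting shift of 1 to 3 points at a 10-point imbalance rests on the assumed source gaps of 10 to 30 points. The attainable gain in power is small, from nothing appreciable at a 10-point gap to about 3 percentage points at 30. Nearly all of it comes from adjusting for source, and stratified allocation adds the balance itself. Stratifying alone would not be a clean repair, because the unadjusted test then falls below its nominal level. The two changes belong together.

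**What to change.** **Allocation.** Replace the sentence on simple randomisation with: computer-generated 1:1 allocation in random permuted blocks of varying size, stratified by recruitment source (SVHM, HCF), run within the study portal with the sequence concealed.

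**Analysis.** State that the primary comparison includes recruitment source whatever the observed balance, for example as a Mantel-Haenszel relative risk stratified by source. This keeps the relative risk already planned.

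**If enrolment has begun.** Leave the allocation as it is and prespecify the source adjustment before any comparison by arm is seen.

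**Cost.** A small change to the portal's allocation list and one added factor in the analysis; the sample size stays at 400. Varying block sizes in an automated system keep assignments hard to predict. One limit remains: source balances stage only in part, because HCF participants range from very early to already applying for surgery funding.

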### Intervention and comparison groups

Participants in the intervention group will receive use of the *SMART Choice* tool at the beginning of the study, as outlined in Table 1. The tool uses patient-focused parameters, including age, sex, body mass index (BMI) and VR-12 survey, to predict the likelihood of improvement after TKA. The predicted outcome is displayed in a format that is similar to the *After My Surgery* tool from the University of York [28]. This format uses a patient-friendly output of how 100 patients who were similar to the user felt after TKA surgery (Fig. 1). All other aspects of the study for participants in the intervention group will be identical to the TAU group.

**Fig. 1 Fig1:**
[figure not shown]
Screenshot of the *After My Surgery* tool for displaying predicted outcome after prognostic tool use. The *SMART Choice* tool will use a similar display format

Participants in the TAU group will receive standard care for TKA consideration without *SMART Choice* tool use. This includes clinic appointments, education packages, and booking/performance of TKA if clinically appropriate. TAU care will vary between institutions.

### Outcomes

The primary outcome for this study is the impact of the *SMART Choice* tool on patient willingness to undergo surgery. This will be measured using a binary question asking the patient if they would be willing to have TKA due to their knee symptoms, as described in Table 2.

**Table 2 Tab2:** Schedule of Assessments (SoA)

	SCHEDULE OF ASSESSMENTS						
	Enrolment	Allocation to intervention	Post-allocation				Close-out
**TIME POINT**	***t***_***x***_	**t**_**0**_	***t***_***1***_	***t***_***2***_	***t***_***3***_	***t***_***4***_	***t***_***y***_
**ENROLMENT:**							
**Eligibility screen**	X						
**Informed consent**	X						
**Allocation to intervention**		X					
**ALLOCATION GROUPS:**							
**Intervention group (I)**		X					
**Treatment as usual group (TAU)**		X					
**INTERVENTION:**							
**Prognostic Tool Use**			I				
**ASSESSMENTS:**							
**Baseline questionnaire**		X					
**Willingness for surgery**		X		X	X	X	X
**Already proceeded with surgery**				X	X	X	X
**Qualitative questionnaires **						X	X

See also Table 3 for definitions and timepoints. I = intervention group. TAU = treatment as usual group. X = participants in both intervention and treatment as usual groups

The secondary outcomes for this study include:Determining the optimal timepoint for prognostic tool use in a patient’s TKA journey to maximise the effect on willingness to undergo surgery.Determine whether there are differences in the effectiveness of the *SMART Choice* tool when used in subpopulations such as sex, gender, and ethnicity.Understanding the user experience and effect on decision making of the *SMART Choice* tool through decision quality questionnaires.

### Participant timeline and assessments

Participants who meet the eligibility criteria will be contacted by the research team via email (Fig. 2). This email will contain a unique link to the study portal and participant access details, including participant username and password. On the study portal, participants will be able to read an electronic copy of the participant information sheet and consent form (PICF) and electronically sign the agreement to participate in the study. Once the PICF is signed, the participant is formally recruited to be part of the study. The study portal will have an in-built function to randomly allocate participants to an arm of the study: intervention or TAU group.

**Fig. 2 Fig2:**
[figure not shown]
Flow diagram describing the study procedure. SVHM: St. Vincent’s Hospital, Melbourne; HCF: Hospitals Contribution Fund Australia; VR-12: Veterans RAND-12; EQ-5D-3L: EuroQol 5 Dimensions 3 Levels; TAU: treatment as usual; K-DQI: Knee Decision Quality Instrument; SURE: decisional conflict screening tool

All recruited participants will be asked to complete a baseline questionnaire within the study portal. This provides an understanding of the participant’s general characteristics. The questionnaire will capture contact details, date of birth, sex, height, weight, comorbidities, medications (analgesia), smoking status, time with knee OA symptoms (years), previous nonoperative management of affected knee OA symptoms, time with knee OA symptoms, consultation with an orthopaedic surgeon in the past, appointment to see an orthopaedic surgeon arranged, previous surgery, previous injury to the affected knee, and presence of contralateral TKA. The baseline questionnaire will also capture the VR-12 and the Euroqol 5 Dimensions 3 Levels (EQ-5D-3L) data to understand the baseline HRQoL utility score for each group.

For participants in the intervention group, the study portal will allow access to the *SMART Choice* tool and provide a predicted outcome for the participant. Inputs onto the tool will be captured electronically; however, the participant will have the option to download a copy of their results for personal reference. Participants in the TAU group will not have access to the *SMART Choice* tool or predicted outcome and will instead continue with the regular assessments for the remainder of the study.

Following the baseline questionnaire (or *SMART Choice* tool use for the intervention group), participants will be asked to complete regular assessments in accordance with the Schedule of Assessments (Tables 2 and 3). This will consist of “willingness for surgery”, “already proceeded with surgery”, and decision quality questionnaires.

**Table 3 Tab3:** Definitions for SoA

Terms	Definitions	
Time Point	***t***_***x***_	Time at initial contact via email with PIS, CF, and eligibiility screen. If a patient is eligible and consents, allocation will immediately follow this time.
	**t**_**0**_	Time at allocation with initial concurrent assessments.
	***t***_***1***_	Immediately after allocation, for prognostic tool use in TAU group.
	***t***_***2***_	6 weeks after initial assessment (t_0_)
	***t***_***3***_	12 weeks after initial assessment (t_0_)
	***t***_***4***_	6 months after initial assessment (t_0_)
	***t***_***y***_	Time at study closure for individual participant. This should be equal to t_4_ if all assessments are completed on schedule.
Baseline Questionnaire	Questionnaire for all patients who have been allocated in the study. Same for all groups. Captures basic demographic data as well as questions about previous knee treatment and surgery. This section will also capture baseline health-related quality of life through the VR-12 and EQ-5D-3L.	
Wilingness for Surgery	This assessment asks the question "Are your knee symptoms so bothersome that you wish to undergo surgery if medically fit to do so?" Yes / No. If yes, "In what time frame are you willing to have surgery?" [Time in months].	
Already Proceeded with Surgery	This assessment asks the question "Have you already received a TKA for your knee symptoms?" Yes / No. The purpose for this assessment is to 1) check if the patient has undergone TKA, and 2) outcome aligns with their willingness for surgery response.	
Qualitative Questionnaires	This assessment consists of K-DQI (decision quality) and SURE (decisional conflict) tools.	

*PIS* participant information sheet, CF consent form, *TKA* total knee arthroplasty, *OA* osteoarthritis, *VR-12* Veterans-RAND 12, *EQ-5D-3L* EuroQol 5 Dimensions 3 Levels, *K-DQI* Knee Decision Quality Instrument, *SURE* decisional conflict screening tool

The initial assessment will be the first timepoint at which regular assessments will be performed. At the end of the initial assessment, participants will be thanked for their time and be reminded of follow-up. Participants will receive emails with access to the study portal at subsequent follow-up periods: 6 weeks, 3 months, and 6 months after recruitment.

Willingness for surgery assessment consists of a single binary question: “Are your knee symptoms so bothersome that you would be willing to undergo surgery if medically fit to do so? (Yes/No)” If yes, “In what time frame are you willing to have surgery?” [Time in months]. The purpose of this assessment is to evaluate whether the patient is still of the mindset to proceed with surgery.

Already proceeded with surgery assessment consists of a single binary question: “Have you already received a TKA for your knee symptoms? (Yes/No).” The purpose of this assessment is to 1) correlate true outcomes for willingness for surgery if applicable and 2) differentiate baseline HRQoL data between knee OA symptoms (if not proceeded with surgery yet) or TKA outcomes. This will not be asked at the initial assessment.

All participants in the intervention group will be sent two additional decision quality questionnaires via email at the time of their final assessment (6 months after recruitment). These questionnaires have been validated from previous research to produce discriminatory and reproducible results [29, 30]. The addition of these questionnaires will provide a cross-sectional understanding of how useful the *SMART Choice* tool was for patient decision-making.

The first questionnaire is the “Knee Osteoarthritis Decision Quality Instrument” (K-DQI) [29]. This questionnaire is specific for patients who suffer from knee osteoarthritis. The questionnaire aims to assess:Which aspects of decision-making matter most to the patientHow well the patient is understanding the information provided, andThe level of communication between the patient and clinician prior to decision-making.

The second questionnaire is a short screening tool to assess decisional conflict [30]. It consists of four binary items using the acronym “SURE” (Table 4).

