**Methods:**

This is a multicentred, pragmatic, randomised controlled trial conducted in Melbourne, Australia. Participants will be recruited from the St. Vincent’s Hospital, Melbourne (SVHM) Orthopaedic Clinic, and the client base of HCF, Australia (private health insurance company). Patients over 45 years of age who have been diagnosed with knee osteoarthritis and considering TKA are eligible for participation. Participants will be randomised to either use the *SMART Choice* tool or treatment as usual. The *SMART Choice* tool provides users with a prediction for improvement or deterioration / no change after surgery based on utility score change calculated from the Veterans-RAND 12 (VR-12) survey. The primary outcome of the study is patient willingness for TKA surgery. The secondary outcomes include evaluating the optimal timing for tool use and using decision quality questionnaires to understand the patient experience when using the tool. Participants will be followed up for 6 months from the time of recruitment.

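### The primary outcome is defined as willingness for TKA, but the printed item asks only about surgery; the item should name the operation (minor)

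*Protocol article*

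**What the plan says.** The abstract states: "The primary outcome of the study is patient willingness for TKA surgery". The Outcomes section says it will be measured by a "binary question asking the patient if they would be willing to have TKA due to their knee symptoms". Both descriptions name TKA.

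The item itself is printed twice, in two wordings:

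- Table 3 (Definitions for SoA): "Are your knee symptoms so bothersome that you wish to undergo surgery if medically fit to do so"
- Text of Participant timeline and assessments: "Are your knee symptoms so bothersome that you would be willing to undergo surgery if medically fit to do so"

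Neither version names TKA or knee replacement. Nor does the question that follows a yes, which asks for a time frame in months. The companion assessment on having already proceeded does name the operation: "Have you already received a TKA for your knee symptoms".

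Table 2 schedules the willingness item at allocation, 6 weeks, 12 weeks and 6 months. The companion item is scheduled at the three follow-up points only.

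**The concern.** A binary primary endpoint rests on how one question is understood. Here the definition is specific to one operation and the question is not. The tool predicts the result of TKA only, so the response it should move is willingness for TKA.

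Applied literally, the item scores two kinds of participant correctly: those willing to have TKA (yes) and those unwilling to have any operation (no). A third kind is scored wrongly: someone who has moved away from TKA but would still accept a different knee operation. That person can truthfully answer yes and is then counted as willing for TKA. The exclusion criteria screen out people who are considering certain other arthroplasties at entry. They do not govern a change of mind over the following 6 months, and they do not list non-arthroplasty knee operations.

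Table 3 also gives checking agreement with the willingness answer as a purpose of the companion item, so a TKA-specific event would be compared with a non-specific answer. No other scheduled item asks which operation a yes referred to, so the ambiguity could not be resolved afterwards.

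**Working it through.** **Step 1. Compare the texts.**

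| Place | Operation named? |
|---|---|
| Abstract, primary outcome | TKA |
| Outcomes, description of the question | TKA |
| Table 3, willingness item | surgery only |
| Text, willingness item | surgery only |
| Months follow-up question | surgery only |
| Companion item, already proceeded | TKA |
| Baseline questionnaire, history | surgery, in the general sense of earlier operations |

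The mismatch between definition and item is a matter of record and needs no assumption.

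**Step 2. Reproduce the planned sample size.** Inputs from Sample size and recruitment: 65% willing against 50%, alpha 0.05, power 0.80, and the stated result, "a sample size of 169 participants in each arm was required based on calculations using a two-sided t-test". Allocation is 1:1.

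With p1 = 0.65, p2 = 0.50 and mean 0.575, the usual two-proportion formula is

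n = [1.96·√(2·0.575·0.425) + 0.8416·√(0.65·0.35 + 0.50·0.50)]² / 0.15²

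= (1.3703 + 0.5816)² / 0.0225 ≈ 169.3, or 170 rounded up. The arcsine version gives 169.1. The stated 169 is reproduced, and power at 169 per arm is 79.9%.

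**Step 3. Illustrate what misclassification would do.** Let q be the share of TKA-unwilling participants who answer yes because they would accept another operation. The protocol gives no value, so q is an assumption. If q is the same in both arms, the recorded rates are

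- TAU: 0.65 + 0.35q
- intervention: 0.50 + 0.50q
- difference: 0.15 − 0.15q = 0.15(1 − q)

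| Assumed q | TAU | Intervention | Difference (points) | Power at 169 per arm |
|---|---|---|---|---|
| 0 | 65.0% | 50.0% | 15.0 | 79.9% |
| 2% | 65.7% | 51.0% | 14.7 | 78.5% |
| 5% | 66.75% | 52.5% | 14.25 | 76.3% |
| 10% | 68.5% | 55.0% | 13.5 | 72.6% |

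**Step 4. Check the direction.** With separate shares, the recorded difference is 0.15 + 0.35·q(TAU) − 0.50·q(intervention). It is smaller than 0.15 only if 0.50·q(intervention) exceeds 0.35·q(TAU), that is, if q(intervention) > 0.7·q(TAU). For example, q(TAU) = 10% and q(intervention) = 5% gives 0.15 + 0.035 − 0.025 = 0.16, which is larger than planned. Equal shares shrink the difference, but the direction is not fixed in general.

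**The case against.** The best defence is that context settles the meaning. Every participant must be considering primary unilateral TKA and must already have tried nonoperative management. Those considering bilateral, revision, unicondylar or patellofemoral procedures are excluded. The article uses surgery as shorthand for TKA throughout, and the Outcomes section passes from one term to the other in consecutive sentences. The assessment titled as having proceeded with surgery asks about TKA, which suggests the authors treat the two as the same. The information sheet and portal screens are not shown and may name TKA around the item. The agreement check is also limited by waiting times: under Study design and setting, patients may wait up to a year for a consultation and another 6–12 months for the operation, so a yes without TKA at 6 months is expected in any case.

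Most of this stands, and it is why the misclassified share is likely to be small. It does not remove the mismatch. The baseline questionnaire uses surgery in the general sense, so the word is not reserved for TKA in the portal. Eligibility also describes intentions at entry, not at later visits.

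A reader might infer that the treatment effect is diluted and the trial underpowered as a result. The protocol does not support that. It gives no misclassified share, the power losses above only restate the assumed q, and the direction depends on the share in each arm.

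**Conclusion.** The point holds as a minor one. What is established is that the primary outcome is defined as willingness for TKA while both printed versions of the item, and the months question, ask only about surgery. What follows is a possibility of misclassification, not a demonstrated bias. If an assumed 2% to 10% of TKA-unwilling participants in both arms were affected, the planned difference would be 14.7 to 13.5 points, with power of 78.5% to 72.6% at 169 analysed per arm. With q near zero, which eligibility makes plausible, the effect is negligible. If the shares differ between arms, the difference could shrink or grow. The planned sample size needs no change on this account.

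**What to change.** The two printed versions already have to be reconciled, because Table 3 says wish and the text says would be willing. In the same edit, replace the bare word surgery with total knee replacement of the affected knee, in both the item and its months follow-up question. Print the result identically in Table 3 and in the text, and use it in the portal at every visit. If any participants have already answered, flag the answers collected before the item was changed.

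The cost is a few words and a minor amendment, with no extra visits, participants or analyses. The one drawback is possibly reduced comparability with earlier studies, if those used a generic surgery item; the article does not show their wording.
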